### Withdrawal from the study

2.24

Any participant may at any time after they have consented decide that they wish to withdraw from continuation in the study (or following advice from a medical professional), which may also include withdrawal of all data and/or blood samples. In line with CONSORT Guidelines^31^ reasons for withdrawal will be recorded.

### End of trial

2.25

The end of trial is the date of the completion of the postintervention focus group. The following criteria will be used to prematurely stop the research:
1.A decision made by the CI or any member of the ST on the grounds of safety issues, such as an unacceptable number of adverse events.2.An evaluation via a fully powered RCT of a similar home‐based HIIT program for PwP. There are currently (last assessed June 21, 2023) no similar trials registered with clinicaltrials.gov.

Figure 3 shows a schematic overview of the HH4P feasibility study participant pathways.

**Figure 3 hsr21800-fig-0003:**
[figure not shown]
Overview of anticipated participant pathways. BDNF, brain‐derived neurotrophic factor; GP, general practitioner; HH4P, HIIT‐Home4Parkinson's; HIIT, high‐intensity interval training; HR_max_, maximum heart rate; OxPAQ, Oxford participation and activities questionnaire; PA, physical activity; STS, sit to stand; UoP, University of Plymouth; UPDRS, Unified Parkinson's Disease rating scale; VO_2max_, maximal oxygen uptake.

### Data analysis

2.26

#### Quantitative analysis

2.26.1

A detailed analysis plan will be developed before any statistical analysis; however, the below provides an overview of the expected plan;
Summary of baseline data and flow of participants.

A CONSORT diagram will provide detailed descriptions of numbers of expressions of interest, meeting eligibility, having baseline data collected, being randomized, receiving the intervention, and having post‐intervention data collected.

Outcome analysis.Analyses of quantitative data will be in two stages:
1.Feasibility outcomes: Data from screening and recruitment will be used to generate estimates of eligibility, recruitment, retention, and consent in the trial population (Objectives ciii and cvii). Adherence data will also be used to assess the acceptability of the HH4P program (Objective Av). Estimation of pre‐ and postintervention completion rates for mechanistic, physiological, and clinical outcome measures will be undertaken along with appropriate confidence intervals (Objective Bii). In addition, Spearman's rank correlation coefficient will be calculated to assess the robustness of each outcome, by comparing pre and postintervention scores (Objective Bii). Furthermore, multiple regression will be used to explore the baseline factors that are most strongly associated with outcomes, to inform potential stratification in a full trial (Objective Civ).2.Mechanistic, physiological, and clinical outcomes: As it is inappropriate to use feasibility study data to formally test for between‐group treatment effects, the mechanistic, physiological, and clinical outcome analyses will primarily be of a descriptive nature, rather than inferential.^17^ Descriptive statistics of the proposed primary and secondary outcomes will be produced, as appropriate for each measure for each trial arm. Interval estimates of the potential intervention effects, relative to usual care only, will be produced in the form of a 95% confidence interval (Objective Bi). Missing data will be imputed using a measure of central tendency to allow ITT analysis.

IBM SPSS software (version 27) and Microsoft Excel (version 2209) will be utilized for quantitative data analysis.

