“HIIT‐Home4Parkinsons” (HH4P) is a novel, patient‐focused, cocreated home‐based HIIT program for PwP. HH4P will be delivered as an adaptable, individualized, 12‐week home‐based HIIT intervention, structured to maximize achievability through remote supervision and the use of appropriate physical and online resources. As previously described,^11^ the development of HH4P was based on the Medical Research Council (MRC) framework for the development and evaluation of complex interventions,^12^, ^13^, ^14^ continually informed by input from patient and public involvement (PPI) contributors and clinicians within a cocreative, iterative planning process of online focus groups and exercise testing. Having now optimally developed the HH4P program, it is critical to undertake a feasibility study before undertaking a definitive trial to address remaining uncertainties. This protocol describes the HH4P parallel‐group randomized controlled feasibility study, developed to evaluate the practicality and utility of the HH4P program, and ultimately inform the development of a full trial designed to facilitate the initial engagement and extended participation in HIIT for PwP.

This feasibility study has three aims.
1.To evaluate the feasibility, safety, and acceptability of a 12‐week home‐based HIIT program for PwP.2.To identify the clinical and physiological outcomes that could be feasible and sensitive to change compared to usual care in a full home‐based HIIT trial for PwP.3.To elucidate the key methodological considerations for the implementation of a full home‐based HIIT trial. Table 1 shows specific objectives relating to each aim.

**Table 1 hsr21800-tbl-0001:** Feasibility study objectives.

Aim	Objectives. Aims will be achieved by determining
A	i. HH4P program safety ii. Adherence to the HH4P exercise program iii. Completion of the HH4P exercise program iv. Achieved exercise intensity v. Acceptance of HH4P exercise program and delivery procedures vi. Practicality of intervention resources vii. Intervention fidelity
B	i. Responsiveness to change in mechanistic, physiological, and clinical outcomes to inform the selection of primary and secondary outcomes for a definitive trial ii. Feasibility of outcome measure procedures (including rates of outcome measure completion) iii. The association between baseline and postintervention scores

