### Sample size

2.5

As this is a feasibility study, an a priori power calculation to detect a significant between‐group difference in a primary outcome is not appropriate.^17^ Instead, this study aims to gain estimates of the likely rates of recruitment and retention, and variability of the proposed primary and secondary outcomes to inform sample size calculations for a potential full trial (objective Cvi). For this feasibility study, we aim to recruit 24 participants^18^ (12 interventions and 12 usual care controls). It is anticipated that to recruit these 24 participants we will need to telephone screen approximately 37 people, of which approximately 35% (*n* = 13) will be found to be ineligible after screening, leaving 24 people to grant consent, and ultimately be randomized. From other similar studies,^19^ we believe that retention rates will be at least 85%, leaving a likely sample at the final follow‐up of between 20 and 24 participants.

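### The pre/post Spearman coefficient cannot show the robustness of an outcome: it misses uniform change, and it can fall for a responsive outcome if arms are pooled or response varies

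*Protocol article*

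**What the plan says.** Section 2.26.1 of the protocol article places the analysis in the first stage, among the feasibility outcomes: Spearman's "rank correlation coefficient will be calculated to assess the robustness of each outcome", from the scores before and after the program, with the tag Objective Bii. It does not define robustness, does not say whether the arms are pooled, and sets no cut-off.

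The Background and Table 1 give the purpose that such a statistic would have to serve:

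- The second aim (B in Table 1) is "To identify the clinical and physiological outcomes that could be feasible and sensitive to change compared to usual care".
- Objective Bi is "Responsiveness to change in mechanistic, physiological, and clinical outcomes to inform the selection of primary and secondary outcomes for a definitive trial".
- Objective Bii is "Feasibility of outcome measure procedures (including rates of outcome measure completion".
- Objective Biii is "The association between baseline and postintervention scores".

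Responsiveness is analysed separately. In the second stage of Section 2.26.1, interval estimates of the intervention effect relative to usual care "will be produced in the form of a 95% confidence interval (Objective Bi". On numbers, Section 2.5 states "we aim to recruit 24 participants", 12 per arm, with 20 to 24 expected at follow-up.

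**The concern.** The sentence ties a named statistic to a named purpose, and the statistic does not fit the purpose. Robustness of an outcome measure would ordinarily mean that it gives stable readings when nothing has changed. A correlation across 12 weeks can speak to that only where no intervention took place. In the HIIT arm it mixes measurement noise with real differences in response. In neither arm can it detect a shift shared by everyone, such as a practice effect on the sit-to-stand or exercise test.

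The aim is to find outcomes that are sensitive to change. A low coefficient may mean a noisy measure, or one that picked up a real response differing between people or between arms. A high coefficient may come from a measure that shifted for everyone. A team choosing outcomes for the full trial that takes rho as a quality score could be pointed the wrong way.

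The objective tag adds to the confusion. Bii concerns feasibility and completion of the measures. The pre/post association is Biii, to which Section 2.26.1 otherwise assigns no analysis.

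**Working it through.** **Inputs from the protocol.** 24 randomized 1:1, 12 weeks between scores, retention of at least 85%. Check: 24 × 0.85 = 20.4, which agrees with the stated 20 to 24 at follow-up, or about 10 to 12 per arm. The protocol states no figure for rho, so there is none to reproduce.

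**Assumed inputs.** The protocol gives no pre/post correlation, effect size or spread of response. I take baseline SD 1, usual-care Pearson correlation r = 0.8 (0.7 and 0.9 as a range), mean HIIT effect d and between-person response SD h, both in baseline SD units, with normal scores.

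**Step 1: uniform shift.** Adding the same constant to every score leaves all ranks unchanged. Twelve simulated scores compared with themselves plus 5 give rho = 1.000. This holds whichever way the arms are handled.

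**Step 2: formulas.** Under the model post = r × baseline + noise + (d + individual response) in the HIIT arm:

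- HIIT-arm Pearson correlation = r / √(1 + h²). The mean effect d does not appear.
- Pooled Pearson correlation = r / √(1 + h²/2 + d²/4).
- Spearman rho = (6/π) × arcsin(Pearson/2), exact for bivariate normal data and approximate for the pooled mixture.

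**Step 3: results for r = 0.8.**

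| Outcome | HIIT-arm Pearson | HIIT-arm rho | Pooled Pearson | Pooled rho |
|---|---|---|---|---|
| Unaffected (d = 0, h = 0) | 0.80 | 0.79 | 0.80 | 0.79 |
| Uniform effect (d = 0.8, h = 0) | 0.80 | 0.79 | 0.8/√1.16 = 0.743 | about 0.73 |
| Varying response (d = 0.8, h = 0.6) | 0.8/√1.36 = 0.686 | 0.67 | 0.8/√1.34 = 0.691 | 0.67 to 0.68 |

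Large simulations agree: 0.786 for the unaffected outcome, about 0.725 pooled for the uniform effect, and 0.668 (HIIT arm) and 0.676 (pooled) for the varying response. Usual-care rho is 0.79 throughout. Other assumed correlations give the same pattern. With a uniform 0.8 SD effect, pooled rho goes from 0.68 to 0.63 at r = 0.7 and from 0.89 to 0.82 at r = 0.9.

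**Step 4: precision.** For a Pearson r of 0.8 at n = 12, Fisher's z is 1.099 and the half-width is 1.96/√(12 − 3) = 0.653. The limits are tanh(0.445) = 0.42 and tanh(1.752) = 0.94. For a Spearman rho of 0.8 the approximate interval is wider, 0.33 to 0.95 at n = 12 and 0.54 to 0.92 at n = 24. Differences of the size in Step 3 would be hard to tell from noise.

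**Step 5: the legitimate use.** In a full trial analysed by ANCOVA, the required size scales with 1 − r², where r is the within-arm Pearson correlation. For an illustrative effect of 0.5 SD at 80% power and two-sided 5%, 63 per arm becomes 63 × (1 − 0.64) = 22.7, so 23, at r = 0.8. At r = 0.7 it is 63 × 0.51 = 32.1, so 33.

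**The case against.** The best defence is that nothing in the protocol acts on rho. It sits among exploratory feasibility outcomes with no threshold or ranking, and the progression criteria in Section 2.32 do not mention it. Responsiveness has its own between-arm interval under Objective Bi. The pre/post association is a declared objective (Biii), so calculating it fulfils the plan. The section calls itself an overview, with a detailed analysis plan to follow. All of this stands.

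It limits two stronger readings that a reader might infer. The first is that the plan will select unresponsive outcomes and discard responsive ones. The text does not say that rho will be used to choose outcomes. The second is that any treatment effect lowers rho. Analysed by arm with a uniform response, rho in the HIIT arm stays at 0.79 whatever the mean effect. The fall needs pooled arms, which the text neither states nor rules out, or a response that varies between people. Nor does pooling always lower rho below the HIIT-arm value: in the varying-response case, pooled rho is slightly higher (0.68 against 0.67).

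The defence does not rescue the robustness reading. The blindness to uniform change holds under every choice of pooling. The later plan could add detail, but it would have to contradict this sentence to correct it.

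**Conclusion.** The point holds as a misuse and mislabelling of a statistic, worth correcting but not a threat to the trial's main conclusions. A pre/post Spearman coefficient over 12 weeks with half the sample treated measures neither reliability nor responsiveness, and its tag should be Biii. That conclusion needs no assumed figures.

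The size of any distortion does rest on assumptions. At a usual-care correlation of 0.8 and a mean effect of 0.8 SD, rho moves from 0.79 to about 0.73 if the arms are pooled and response is uniform. It moves to about 0.67 or 0.68 if response varies with SD 0.6, and not at all if the arms are separate and response is uniform. The risk is that the robustness label misleads those choosing outcomes for the full trial, not that it settles the choice.

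**What to change.** Replace the sentence in Section 2.26.1, or correct it in the detailed analysis plan, as follows:

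1. Tag the pre/post association as Objective Biii and remove the reference to robustness.
2. Report the correlation by arm, or adjusted for arm, with a 95% confidence interval. Use Pearson where it is to inform an ANCOVA-based sample size (Objective Cvi). Under normality the difference is small (0.80 against rho 0.79), but Pearson is the quantity in the formula.
3. Estimate stability from the usual-care arm only, by the intraclass correlation and within-person SD, each with a confidence interval. Unlike rho, an absolute-agreement intraclass correlation also registers a systematic shift.
4. Judge responsiveness by the between-arm interval already planned for Objective Bi.

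The data are already to be collected, so the cost is a few lines of text and minor programming. The downside is that stability would rest on about 10 to 12 people over 12 weeks and will be imprecise, as the interval of 0.42 to 0.94 for r = 0.8 at n = 12 shows. Reporting the interval makes that plain.

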### Study design overview

2.1

This is a randomized controlled parallel group feasibility study with mechanistic, physiological, and clinical subcomponents. Twenty‐four PwP will be randomized in a 1:1 ratio either to the HH4P 12‐week, home‐based HIIT program plus usual care (intervention) or to usual care alone (control). Assessments will include feasibility and safety factors, and pre and postintervention assessments of potential primary and secondary outcomes undertaken by assessors blinded to group allocation. Both groups will undergo objective physical activity (PA) monitoring 1 week before, and in Week 7 of the intervention. Exercise participants will be invited to attend a posttrial focus group constituting a qualitative addition to assessment of intervention fidelity.

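### Filling missing outcomes with a mean or median understates the SD of the filled variable and makes the 95% CI too narrow, in a study meant to estimate variability; if filled data size the full trial, it can be mis-sized in either direction

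*Protocol article*

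**What the plan says.** Section 2.26.1 (Quantitative analysis) has two stages. Stage 1 covers feasibility outcomes, including the pre-post association: "Spearman's rank correlation coefficient will be calculated to assess the robustness of each outcome, by comparing pre and postintervention scores". Stage 2 covers the mechanistic, physiological and clinical outcomes. It gives descriptive statistics per arm and a 95% confidence interval for the effect relative to usual care (Objective Bi), and it closes with: "Missing data will be imputed using a measure of central tendency to allow ITT analysis".

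The sentence does not say whether the fill is a mean or a median, per arm or pooled, or applied to the post score or to the change score.

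Section 2.5 (Sample size) explains that, in place of a power calculation, the study will estimate recruitment, retention and "variability of the proposed primary and secondary outcomes to inform sample size calculations for a potential full trial" (Objective Cvi). It also gives the expected loss: "we believe that retention rates will be at least 85"%, leaving a final sample "of between 20 and 24 participants". Section 2.15 defines the proposed primary outcomes as changes from baseline.

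**The concern.** A filled value sits at the centre of the distribution. It contributes nothing, or almost nothing, to the sum of squares, but it counts as a full observation in the denominator, in the standard error and in the degrees of freedom. The SD falls and the standard error falls further.

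The stated reason does not call for this. Intention to treat means analysing people in the arm to which they were randomised. Section 2.19 already provides for that by collecting outcomes regardless of adherence. A constant fill adds no information about those who are lost; it makes the interval look as if all 24 had been measured.

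Two of the study's products are at stake: the 95% CI for the effect, which comes from the same stage as the imputation rule, and the variability estimates that section 2.5 wants for planning the full trial.

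**Working it through.** **Plan's own figures first (section 2.5).** 37 × 0.35 = 12.95, stated as 13 ineligible. 37 × 0.65 = 24.05, stated as 24 randomised. 24 × 0.85 = 20.4, stated as a lower limit of 20. All reproduce. With 12 per arm and balanced loss, the expected range is 10 to 12 observed per arm.

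**Assumptions, not in the document.** Arm-mean fill, loss completely at random and balanced, normal outcomes with SD 1, and pre-post correlation r. For the full-trial illustration: two-sided alpha 0.05, standardised difference 0.5, power 80% or 90%.

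**SD of the filled variable.** With m of 12 observed per arm, the variance is multiplied by f = (m − 1)/11.
- m = 12: f = 1, no effect.
- m = 11: f = 10/11 = 0.909; SD factor √0.909 = 0.953.
- m = 10: f = 9/11 = 0.818; SD factor √0.818 = 0.905.

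**Width of the 95% CI when the analysed variable is filled.**
- Filled half-width: t(22) × √f × √(2/12). At m = 10: 2.074 × 0.905 × 0.408 = 0.766 SD.
- Observed-data half-width: t(2m − 2) × √(2/m). At m = 10: 2.101 × 0.447 = 0.940 SD.
- Ratio 0.766/0.940 = 0.815, about 18% narrower. At m = 11: 0.807/0.889 = 0.908, about 9% narrower.

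**Coverage.** The point estimate equals the observed-data difference, so coverage is P(|t| < t(22) × √f × √(m/12)) on 2m − 2 degrees of freedom. At m = 10 the limit is 2.074 × 0.905 × 0.913 = 1.712 on 18 df, giving 89.6%. Simulation (5,000 runs at each of four values of r) gave 89.1 to 89.7% filled, against 94.8 to 95.4% on observed data.

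**If only the post score is filled and change is then computed.** The per-arm variance of the mean change is reported as (1 + f − 2rf)/12. Its true value is 1/10 + 1/12 − 2r/12. At r = 0.7 and m = 10 these are 0.0561 and 0.0667, ratio 0.84. The uncertainty of the effect is still understated, by about 16% in variance.

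**Full-trial size, if filled data were used (m = 10).**

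| Sized on | n relative to correct | Result |
|---|---|---|
| Imputed post-score SD, or change SD with change itself imputed | f | 0.818: about 18% too small |
| Change computed from filled post scores | (1 + f − 2rf)/(2 − 2r) | 1.00 at r = 0.5; 1.12 at r = 0.7; 1.27 at r = 0.8 |
| ANCOVA | f(1 − fr²)/(1 − r²) | 0.87 at r = 0.5; 0.96 at r = 0.7; 1.01 at r = 0.75; 1.08 at r = 0.8 |

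For the first row, n per arm = 2(1.96 + z)²/0.5². At 90% power this is 84.1, so 85, against 84.1 × 0.818 = 68.8, so 69 (true power 83.6%). At 80% power it is 63 against 52 (true power 72.2%). The ANCOVA ratio crosses 1 where r² = 1/(1 + f) = 0.55, so r is about 0.74.

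**Spearman, only if the filled data are used (m = 10).** The mean coefficient falls from 0.459 to 0.410 at r = 0.5, and from 0.759 to 0.679 at r = 0.8.

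**Pooled-mean fill.** Each arm's mean is pulled to the common mean for 2 of 12 people, so the estimated effect is multiplied by 10/12: it shrinks by one sixth.

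**The case against.** The strongest reply has four parts.

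1. *The direction of a sizing error is not fixed.* A reader might infer that the full trial would be undersized. The document does not support that. It does not say that the SD for the sample size comes from filled data, nor whether the trial would be sized on post scores, change or ANCOVA. The proposed primary outcomes are changes from baseline, and filling only the post score inflates the change SD once r exceeds 0.5. An attenuated correlation also raises an ANCOVA sample size. This objection stands.

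2. *The reach of the rule is limited.* A reader might also infer that the pre-post correlations are computed on filled data. The Spearman analysis belongs to stage 1 and the imputation sentence closes stage 2; nothing links them. This stands too. Only the link to the 95% CI is direct. The link to the SDs is a reasonable inference from the per-arm descriptive statistics and section 2.5.

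3. *Two missing per arm is the floor of the plan's range.* True: the effect roughly halves at 1 of 12 and vanishes with complete data.

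4. *The analysis is mainly descriptive, and a detailed analysis plan is still to come.* This lowers the urgency, since no formal test depends on the rule and the feasibility and safety results are untouched. It does not rescue the rule. The sentence is a stated commitment to a method, not a detail left open, and an interval in a descriptive analysis should still carry its nominal coverage.

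**Conclusion.** The concern holds in limited form and should be fixed. Single imputation by a mean or median understates the SD of the filled variable and the uncertainty of the between-arm effect, intention to treat does not need it, and it works against the aim in section 2.5.

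At the lower retention limit, with the fill applied to the analysed variable, the SD factor is 0.905, the CI is about 18% narrower and coverage is about 89 to 90%. These figures assume arm-mean filling and balanced, completely random loss.

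The consequence for the full trial is conditional: if filled data were used, n could be about 18% too small (imputed post-score or change-score SD), about 4% too small (ANCOVA, r = 0.7), or about 12% too large (change from filled post scores, r = 0.7). That the sign depends on choices the article leaves open is a further reason not to use such values for planning. Attenuated correlations, and an effect shrunk by one sixth, arise only under readings that the text neither states nor excludes.

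**What to change.** Replace the imputation sentence in section 2.26.1 so that it provides as follows:

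- SDs and pre-post correlations are estimated from observed values, with the number analysed reported for each outcome.
- The 95% CI for the effect comes from observed data with participants in their randomised arm, using a baseline-adjusted model, or a mixed model for baseline and post scores that keeps everyone with a baseline value.
- Any multiple imputation is a sensitivity analysis.
- Singly imputed values are not used for the full-trial sample size.

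This changes one sentence before the detailed analysis plan is written and needs no new data. The price is slightly wider intervals whenever data are missing.
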